To evaluate the effect of the intervention on executive function we will conduct the analysis based on the pre-training (baseline) and post-training data. Finding a significance level of *p* < 0.05 on the primary executive function outcome measure will support that the intervention improves executive function in the population.

To evaluate the endurance of effects following completion of the intervention we will conduct the analysis based on the pre-assessment (baseline) and follow-up assessment data. We will conduct confirmatory analyses based on the post-assessment (completion) and follow-up assessment data to evaluate the magnitude of change (further increase or decline) over the no-contact follow-up period.

To evaluate and identify specific populations of treatment responders and non-responders we will conduct exploratory data analyses post-hoc to examine predictors of treatment gain and predictors of lack of treatment gain based on baseline participant demographic, cognitive, and functional measures, as well as on learning rate and plateau performance measures derived over the course of the intervention usage. We will initially employ single regression models to identify variables that predict change in cognitive and functional assessments, and then use generalized linear modeling to explore combinations of predictors of treatment gain or lack of gain.

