The current study is designed to the highest standard of RCT (e.g., blinded and deals with appropriate allocation concealment). Moreover, this protocol will measure immediate as well as lasting benefits of treatment. Lastly, many previous studies lacked statistical power due to a small sample size. ALERT is appropriately powered to detect improvements in targeted cognitive operations. We have statistically powered the study to detect a between groups Cohen’s d effect size of 0.50 on an outcome measure, calculated as the between group difference in the treatment effect means (post-assessment score minus pre-assessment score) divided by the pooled standard deviation of the observed test-retest reliability. This effect size translates, for example, in an improvement of 5.8 points (on an IQ-like index score) within the treatment group versus an improvement of 1.0 point within the active control group, with both groups showing a variance of 10 points (2/3 of a standard deviation, as observed in other composite cognitive performance data) from pre-assessment to post-assessment. Recently published studies that examined the efficacy of the core exercise (TAPAT) in participants with acquired brain injury (*n* = 40) documented effect sizes of 0.75 [32] and 0.69 [33] on the composite attention measure; we believe this is a reasonable estimate of the plausible effect size in this trial. Also, a recent meta-analysis of the effect size of cognitive rehabilitation documented an average between groups effect size of 0.31 [58] in the population of studies used to support the practice guidelines for cognitive rehabilitation [59, 60]. Based on this analysis, we will enroll 120 participants into the trial. We intend to enroll equally from each site (60 per site).

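### The exploratory responder analysis looks for predictors of treatment gain by regressing on change and names no predictor-by-arm interaction, so as written it finds predictors of any change

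*Protocol article*

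**What the plan says.** The responder analysis is in the last paragraph on analysis methods in the Data analysis section, after the list of secondary outcomes. Its aim is given as "To evaluate and identify specific populations of treatment responders and non-responders", and its status is clear: "we will conduct exploratory data analyses post-hoc to examine predictors of treatment gain and predictors of lack of treatment gain".

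Two groups of predictors are named. One is "based on baseline participant demographic, cognitive, and functional measures". The other is "learning rate and plateau performance measures derived over the course of the intervention usage".

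The method has two steps. First: "We will initially employ single regression models to identify variables that predict change in cognitive and functional assessments". The authors will "then use generalized linear modeling to explore combinations of predictors of treatment gain or lack of gain" as the second step. Neither step mentions arm or an interaction between arm and predictor, and the paragraph does not say which arms enter the regressions. For the efficacy analyses, by contrast, the same section makes the group-by-time interaction the deciding term.

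**The concern.** A predictor of treatment gain is a characteristic on which the difference between the arms depends. A regression of change on one predictor estimates something else: how change of any origin varies with that predictor. Practice effects and natural course are included, and both can occur under the active control. The article's own sample-size example gives the control arm a 1.0-point improvement.

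A second problem affects some of the predictors. The Repeated assessment battery section says that the baseline battery is given again at V2 and V3, so the baseline cognitive and functional measures are the same tests whose change is the response. Change is the later score minus the baseline score. A test's own baseline is therefore negatively correlated with its change even if treatment has no effect, or has the same effect on everyone. The direction of this artefact is known in advance: lower baseline, larger apparent gain. A finding of that form could be read as evidence about who should be offered the training.

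**Working it through.** The article gives no sample size, power or error rate for this analysis, so there is no stated figure to reproduce. The check asks how often the planned single regression would be significant when no characteristic modifies the treatment effect.

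**Inputs**
- Spread of change, from the Strengths section: "both groups showing a variance of 10 points (2/3 of a standard deviation". This gives 10 points on a scale with SD 10 / (2/3) = 15.
- The 10 has to be read as an SD. The example contrasts gains of 5.8 and 1.0 points, and (5.8 - 1.0)/10 = 0.48, close to the stated effect size of 0.50. Read as a variance, the SD would be √10 = 3.16 and the effect 4.8/3.16 = 1.52.
- 60 participants per arm, 120 in total (Overall design and timeline).
- Significance at p < 0.05 (Data analysis); two-sided is assumed here.
- Equal pre and post SDs, normal scores and no dropout are assumed.

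**Test-retest correlation**

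Var(change) = 2·SD²·(1 - r), so r = 1 - SD_change²/(2·SD²) = 1 - 100/450 = 0.778.

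**Correlation of a baseline score with its own change**

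Cov(baseline, change) = r·SD² - SD² = -(1 - r)·SD². Dividing by the two SDs gives corr = -√((1 - r)/2) = -√(0.222/2) = -0.333.

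**Chance of p < 0.05 with no effect modification** (Fisher z, standard error 1/√(n - 3))
- n = 60: atanh(0.333)·√57 = 0.3466 × 7.550 = 2.617; Φ(2.617 - 1.960) = 0.74.
- n = 120: 0.3466 × 10.817 = 3.749; Φ(3.749 - 1.960) = 0.96.
- n = 60, r = 0.70: corr = -0.387, about 87%.
- n = 60, r = 0.90: corr = -0.224, about 40%.

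**Simulation check** (4,000 runs, 60 per arm, the same treatment effect for everyone)

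| r | Change on own baseline, TAPAT arm only | Same, both arms pooled | Arm-by-baseline interaction |
|---|---|---|---|
| 0.60 | 96% | >99% | 4.5% |
| 0.70 | 87% | 99% | 5.8% |
| 0.778 | 75% | 95% | 4.8% |
| 0.80 | 71% | 93% | 4.7% |
| 0.90 | 42% | 64% | 5.0% |

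The simulation agrees with the formula. The pooled figures are slightly lower because the simulated treatment effect adds spread to the pooled change scores. Pooling the arms without an interaction makes the artefact easier to detect; it does not remove it. The interaction returns the error rate to about 5%.

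**Where the artefact does not arise**

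A predictor correlated 0.3 with both the pre and the post score, simulated with n = 60 and r = 0.778, was significant in 5.2% of runs. Regression to the mean is therefore a problem for an outcome's own baseline and for measures sharing its error, not for every predictor on the list.

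**The case against.** The strongest reply is that this is a labelled exploratory analysis in a condensed article, and that the arms, covariates and interaction terms belong in an analysis plan that is not shown. Part of this stands. A reader might infer that the control arm is left out; the paragraph does not say so, and its silence on which arms enter is not a fault in itself. A reader might also take the analysis to be single-predictor throughout, but the single regressions are only a first screen before combinations are modelled.

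The reply does not remove the point. The response variable, the type of predictor and the first-step model are stated, and a regression with one predictor cannot contain an interaction. The second step names none either. Fitting the regressions in each arm and comparing slopes would answer the question, but no such comparison is described. The exploratory label covers multiplicity and imprecision; it does not cover a bias of known direction.

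Two further objections stand as limits on size. The correlation of 0.78 comes from an illustration on an IQ-like index, attributed to other composite data, and is not an estimate for this trial's outcomes. The article also does not say that each outcome's own baseline will be used as a predictor of its change, although its wording includes that case.

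**Conclusion.** The concern holds as a minor point. The method as written cannot separate predictors of treatment gain from predictors of change in general. For an outcome's own baseline, or a measure sharing its error, regression to the mean gives a correlation with change of about -0.33 and nominal significance in about 74% of null analyses at n = 60 and 96% at n = 120. At n = 60 the range is 40% to 87% for test-retest correlations of 0.90 down to 0.70. These figures rest on the sample-size illustration, equal pre and post SDs, two-sided testing at 0.05 and no dropout.

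Three stronger readings are not supported:
- That regression to the mean affects every predictor. Demographic variables are not automatically affected. The difficulty with learning rate and plateau is a different one: they are measured after randomisation, during use of the program, with no stated control-arm counterpart.
- That a false responder finding will be reported. The document supports only that one is likely to appear if own-baseline predictors are used.
- That the trial's efficacy conclusions are at risk. They rest on the group-by-time interaction and are unaffected.

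**What to change.** State that both arms enter the responder analysis together. Model the V2 score on baseline score, arm, predictor and predictor-by-arm interaction, and take the interaction as the evidence for a predictor of treatment gain. Where the predictor is the outcome's own baseline, the terms are baseline, arm and baseline-by-arm. Report learning rate and plateau measures as associations within the TAPAT arm only, not as predictors of treatment response.

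This changes analysis wording and needs no new data or visits. The cost is precision: interaction estimates will have wider intervals than the single regressions, and with 60 per arm many will be inconclusive. That width reflects what the trial can say about who benefits.

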### Sharing research results

We will share the overall study results with all participants who enrolled in the study when such results are completed and accepted for publication. We will create a lay-person oriented summary of study results to be mailed to each participant at the end of the trial. At enrollment, two pieces of information are collected that, if appropriate, we will share with the participant to ensure they are receiving appropriate health care, include depression status, and suicidal intent. Any participant screening positive for any of these medical issues will be referred to ensure they are receiving appropriate treatment. We do not intend to share individual assessment data with participants, as the assessment battery is not intended to be the type of comprehensive battery a rehabilitation psychologist would use to guide treatment. Any participant interested in such comprehensive assessment will be referred to an appropriate clinician.

## Discussion

Several therapeutic approaches to improve age-related cognitive decline have been developed, including compensatory strategies (e.g., mnemonic memory aids [51], working memory skills [52, 53], speed of processing [54, 55], perceptual learning [9, 56], and multitasking [57] among others [58]. However, few cognitive training approaches have directly targeted alertness in older adults [25] and long term effects are unclear. In the current study, we will examine whether a novel alertness training approach (TAPAT) will benefit attention and executive functions in older adults, as previously shown in acquired brain injury. We hypothesize that the TAPAT group will show greater benefits in these cognitive domains relative to an active control group and that these benefits will transfer to improvements in functional abilities. The ALERT protocol will also help determine whether TAPAT is effective in creating lasting deficit reductions and functional improvements that contribute to an improved standard of care.

### Strengths

TAPAT targets a key neuromodulatory function, alertness, that is fundamental to many lower- and higher-order cognitive operations known to decline in older adults. Further, the vitality of neuromodulatory centers have been shown critical for neuroplasticity. Thus, improving cognitive function and instigating lasting neurological changes is dependent on maintaining a vital level of alertness. Our previous studies have shown that TAPAT is effective in improving spatial and non-spatial attention, as well as executive functions (e.g., set switching) for a wide range of older adults. In addition, TAPAT is simple to perform, easy to remotely monitor (e.g., by a clinician), and is well tolerated by older adults. Because of these qualities, TAPAT is highly scalable (i.e., administration via any Internet connected device), and thus can be readily administered to many older adults with cognitive decline.

The current study is designed to the highest standard of RCT (e.g., blinded and deals with appropriate allocation concealment). Moreover, this protocol will measure immediate as well as lasting benefits of treatment. Lastly, many previous studies lacked statistical power due to a small sample size. ALERT is appropriately powered to detect improvements in targeted cognitive operations. We have statistically powered the study to detect a between groups Cohen’s d effect size of 0.50 on an outcome measure, calculated as the between group difference in the treatment effect means (post-assessment score minus pre-assessment score) divided by the pooled standard deviation of the observed test-retest reliability. This effect size translates, for example, in an improvement of 5.8 points (on an IQ-like index score) within the treatment group versus an improvement of 1.0 point within the active control group, with both groups showing a variance of 10 points (2/3 of a standard deviation, as observed in other composite cognitive performance data) from pre-assessment to post-assessment. Recently published studies that examined the efficacy of the core exercise (TAPAT) in participants with acquired brain injury (*n* = 40) documented effect sizes of 0.75 [32] and 0.69 [33] on the composite attention measure; we believe this is a reasonable estimate of the plausible effect size in this trial. Also, a recent meta-analysis of the effect size of cognitive rehabilitation documented an average between groups effect size of 0.31 [58] in the population of studies used to support the practice guidelines for cognitive rehabilitation [59, 60]. Based on this analysis, we will enroll 120 participants into the trial. We intend to enroll equally from each site (60 per site).

#### Weaknesses

There are also potential limitations. Due to the long duration and multiple components of our study, attrition rates may pose a potential limitation. Furthermore, lack of motivation could prevent timely completions of the self-initiated training program. With a standardized protocol, frequent check-ins, and regular feedback from our research assistants, we aim to limit dropout rate.

## Abbreviations

C-SSRS: Columbia-Suicide Severity Rating Scale
ITT: Intent-To-Treat
SF-12v2: Short Form 12
TAPAT: Tonic and Phasic Alertness Treatment
